### Intervention

After conducting a survey in patients from the Dutch association of cancer patients’ organizations, the online self-help training “Less fear after cancer” was developed by the Helen Dowling Instituut, an institute for psycho-oncology in Bilthoven, the Netherlands.

“Less fear after cancer” is a tailored online self-help training based on cognitive behavioural therapy. Participants start the training by filling out the FCRI [3], after which they get (automated) feedback about their scores and a suggestion about which modules to follow. The FCRI and all modules are visible on worksheet of the intervention (see Fig. 1). First, participants follow two basic modules: 1) Psycho-education about FCR, its symptoms and learning to recognize symptoms of fear; and 2) The basic principles of cognitive behavioural therapy (this module is divided in two parts). After these basic modules women can choose from the following four the modules that are relevant to their situation: 1) How to stop rumination, behavioural techniques to stop ruminating; 2) Action, making an action plan about what one can do when fear of recurrence pops up; 3) Relax, audio files with relaxation practices; and 4) Reassurance, how and when to seek reassurance. Each module consists of an informative part and a practical part in which participants are motivated to do exercises or assignments in daily life. Participants are advised to take a week for each module they choose, so most participants will need four to six weeks depending on how many modules they do. It is explained that the more time they invest, the more effect they can expect from the training, but participants eventually choose themselves how much time is actually spent on the training. For every patient, the intervention will be available for three months.

**Fig. 1 Fig1:**
[figure not shown]
Screenshot of the “Less fear after cancer” online self-help training

The most important functionality of the online self-help training “Less fear after cancer” is the worksheet, because it gives an overview of the modules and access to the intervention. By clicking on a module, participants can access the information (texts, videos, audio files) and exercises of the self-help training. Other functionalities include a library with the information and forms in pdf format, videos, audio files, and a mailbox for technical assistance.

“Less fear after cancer” is fully automated and primarily non-guided and is delivered without professional support from a therapist. In this study, personal online support by an e-mail coach (the researcher) is available for the women that indicate a need for this. The e-mail coach can give technical assistance and eventually refer participants to their general practitioner or medical specialist when they indicate a need for professional help.

### Usual care

The control group of this RCT has access to usual care. Care as usual may differ somewhat between hospitals and may include psychosocial care from within the hospital or elsewhere. In the Medical Consumption Questionnaire, use of psychosocial care will be assessed. Care as usual will be available in both conditions, in the intervention condition the online self-help is extra.

### Outcomes

All participant outcomes will be gathered using online self-report questionnaires hosted by SurveyMonkey.com. Participants will receive an invitational e-mail with a link to complete the questionnaires online. The questionnaires at baseline, 3 months, 9 months, and 24 months include questions on socio-demographic and medical variables.

### Primary outcomes

*Fear of cancer recurrence* will be assessed using the 43-item Dutch version of the FCRI [3]. The FCRI consists of statements rated on a 5-point Likert scale ranging from 0 (not at all or never) to 4 (a great deal or all the time). The FCRI includes seven subscales: triggers, severity, psychological distress, coping strategies, functioning impairments, insight, and reassurance. The triggers-subscale evaluates the presence of potential stimuli activating FCR. Psychological consequences of FCR are evaluated by the subscales psychological distress and functioning impairments. The insight scale measures the level of self-criticism towards FCR intensity. The reassurance- and coping strategies-scales measure a variety of coping strategies than can be used to cope with FCR including denial, wishful thinking, cognitive avoidance, and reassurance. The severity subscale assesses the presence and severity of intrusive thoughts or images associated with FCR and this scale can be used separately as a brief screening instrument of FCR and as an outcome measure [3]. The severity subscale is the primary outcome measure. The coping strategies- and functioning impairments-scale scores at baseline will be used in the predictor analysis. The original 42-item French-Canadian version of the FCRI had a good internal consistency (Cronbach’s α = 0.95 for the total score and α = 0.89 for the severity subscale) and stable over a 1-month interval (*r* = 0.89, *p* < 0.001) [3]. The scale has a robust factor structure and the results support construct validity with other self-report scales assessing FCR (r’s 0.68 to 0.78) or related constructs (r’s 0.43 to 0.66) and quality of life (r’s −0.20 to −0.36) [3]. The Dutch version of the FCRI (FCRI-NL) is currently being validated.

*Fear of cancer recurrence* will also be assessed with the Dutch version of the Cancer Worry Scale (CWS) [43]. The CWS assesses concerns about developing cancer or developing cancer again and the impact of these concerns on daily functioning. The Dutch version of the CWS consists of 8 items that are rated on a 4-point Likert scale ranging from 1 (never) to 4 (always). Higher scores indicate more frequent worries about cancer. A cut-off score of 13 (low ≤13, high ≥14) turned out to be optimal for detecting severe levels of FCR [44]. Moreover, the CWS is a reliable questionnaire (Cronbach’s α = 0.87) and evidence has been found to support the construct validity [44].

### Secondary outcomes

*Healthcare costs* will be assessed with the Medical Consumption Questionnaire (MCQ), a questionnaire to assess non-disease specific healthcare costs [45]. More precisely, the volume of used healthcare will be assessed with the MCQ. Afterwards, the Dutch Manual on Cost Investigations will be used to calculate the healthcare costs [46].

Furthermore, the Dutch translation of the EuroQol-5D (EQ-5D), a generic measure of health status, will be used for the economic evaluation [47, 48]. The EQ-5D comprises five domains: mobility, self-care, usual activities, pain/discomfort, and anxiety/depression. Each domain consists of one question with three answer categories: (1) no problems, (2) some problems, and (3) extreme problems [47]. A health state can be derived by combining the scores from each dimension [47]. This results in a 5-digit number, for example state 12233. This health state indicates no problems with mobility, some problems with self-care and usual activities, and extreme problems with pain/discomfort and anxiety/depression [47, 48]. EQ-5D health states may be converted into a EQ-5D index by applying predetermined weights to the five domains [49]. The Dutch EQ-5D tariff will be used to value this EQ-5D index [47]. The EQ-5D index gives a societal-based global quantification of the patient’s health status on a scale ranging from 0 (death) to 1 (perfect health) [50]. For economic evaluation, the EQ-5D index scores will be used to determine quality-adjusted life years (QALYs) [50]. Patients will also be asked to rate their overall health status on a visual analogue scale (EQ-5D VAS), a quantitative self-rating of health status in which patients are asked to rate their current health state on a 0 (worst imaginable health status) to 100 (best imaginable health status) scale [48]. The EQ-5D is a ‘user-friendly’ questionnaire, with acceptable reliability and validity for various populations [51–53].

*Psychological distress* will be assessed with the corresponding subscale of the FCRI-NL [3].

### Process outcomes

In addition to the self-report questionnaires, technical data on the use of the intervention will be gathered in the intervention group. For example, frequency of logins, duration of logins, and website activity will be evaluated.

### Other outcomes

The *use of extra (psychological) help* will be assessed with the Medical Consumption Questionnaire (MCQ) [46]. Furthermore, help or referral by the e-mail coach will be registered and added to the MCQ score.

*Psychosocial problems* and risk factors will be assessed with the Psychosocial Distress Questionnaire-Breast Cancer (PDQ-BC) [54]. The PDQ-BC is a multi-dimensional screening instrument specific for breast cancer patients. It consists of nine subscales using 35 items assessing psychological risk factors (i.e. trait anxiety and (lack of) social support) and state anxiety, depressive symptoms, social problems, physical problems, body image, financial problems, and sexual problems. All items are answered on a 4-point Likert scale, ranging from 1 (not at all) to 4 (very much) [54]. For most subscales, high scores indicate more psychosocial problems, except for body image and social support for which higher scores indicate fewer problems [55]. The PDQ-BC appears to have a sufficient internal consistency, and good construct validity, test–retest reliability, and sensitivity to change. Furthermore, the PDQ-BC subscales state anxiety and depressive symptoms have a satisfactory sensitivity and specificity [54–56].

*Self-efficacy for online self-help* will be assessed with a questionnaire which was especially assembled for the current study. Bandura [57] argued that all-purpose measures of perceived self-efficacy usually have limited explanatory and predictive value because most of the items in an all-purpose test may have little or no relevance to the domain of functioning. Scales of perceived self-efficacy should be tailored to the particular domain of functioning that is the object of interest. Therefore, we collected many potentially useful items from various self-efficacy questionnaires [58–62]. In consultation with both professionals and patients, we improved and reduced the items to a 15 item questionnaire tailored to assess self-efficacy for our online self-help training. The items are rated on a 5-point Likert scale, ranging from 1 (not like me) to 5 (totally like me). The items are divided in three domains: 1) general internet use (3 items); 2) health related coping strategies (7 items); and 3) patients’ expectations on online self-help training for fear of cancer recurrence (5 items).

A subsample of patients (*n* = 16) will be asked about their experience with the online self-help in a semi-structured interview, to evaluate the online self-help training and to detect possible ways to further improve the training. There are different profiles of FCR, which vary according to its severity and the type of coping strategies used. Patients will be selected based on their baseline score on the FCRI and will represent different FCR-profiles: mild FCR-severity and low coping, mild FCR-severity and high coping, moderate FCR-severity and high coping, moderate FCR-severity and low coping [63]. From the first 50 participants who finished the online self-help training, four participants from each FCR-profile group will be randomly picked. If women refuse to participate, another participant will be randomly picked from that group.

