#### Cost-effectiveness analyses

The economic evaluation will consist of a cost-effectiveness analysis and a cost-utility analysis, both done from a societal perspective [50]. The cost-effectiveness ratio will represent the costs per significantly improved participant, while the cost-utility analysis will represent the costs per additional quality-adjusted life year (QALY). The time horizon will be life time. As the study period is limited in time, cost and effect will be modelled in time, using the assumption that the spontaneous recovery is 2 years. The effects of this assumption on the cost-effectiveness ratio will be tested by testing the scenarios of spontaneous recovery after 6 months, 1 year and 5 years.

Costs will be estimated from a societal perspective and will thus include the costs related to the intervention, all other healthcare costs and non-healthcare costs during the time horizon of the study. Healthcare consumption will be measured with the MCQ. Healthcare consumption includes all non-disease specific healthcare used in the previous 3 months, such as visiting the general practitioner or other healthcare providers, emergency room visits, hospitalisation, and medication use. Then, the guidelines as descripted by the Dutch Manual on Cost Investigations will be used to calculate the healthcare costs [46]. For healthcare where no guideline or standard prices are available, real cost prices will be determined or, when available, derived from the health care provider administration.

QALYs will be calculated from EQ-5D health states using the Dutch EQ-5D tariff [47]. Non-parametric bootstrap simulations will be used to estimate uncertainty intervals around the ICERs, in order to deal with the most likely skewed distributions of costs. Cost-effectiveness acceptability curves will be calculated to show the probability that the intervention is cost-effective in comparison with the control group, given varying thresholds for the willingness-to-pay for gaining one unit of effect, i.e. a QALY or a significantly improved participant. The robustness of the results will be explored using one-way sensitivity analyses in which the input variables for assessing both cost and effectiveness are varied.

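### Adding e-mail-coach help and referrals to the MCQ score means that use of extra help is not measured like for like in the two arms, and a referral can be counted twice

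*Protocol article*

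**What the plan says.** Under Other outcomes, the protocol article measures use of extra (psychological) help with the MCQ and then fixes a scoring rule: "help or referral by the e-mail coach will be registered and added to the MCQ score".

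The coach is introduced in the Intervention section, where "personal online support by an e-mail coach (the researcher) is available for the women that indicate a need for this". The same section gives the coach's tasks: "The e-mail coach can give technical assistance and eventually refer participants to their general practitioner or medical specialist". The Usual care section states the difference between the arms: "Care as usual will be available in both conditions, in the intervention condition the online self-help is extra". It adds that "In the Medical Consumption Questionnaire, use of psychosocial care will be assessed".

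The MCQ has a second use. Under Cost-effectiveness analyses, "Healthcare consumption will be measured with the MCQ", and the content listed there covers items "such as visiting the general practitioner or other healthcare providers, emergency room visits, hospitalisation, and medication use", with a recall period of three months. That section lists intervention costs as a component separate from other healthcare costs. Under Process outcomes, technical data on use of the training are already collected in the intervention group.

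**The concern.** An outcome that may be compared between randomised arms should be ascertained with the same instrument in both. Here the instrument is self-report in one arm, and self-report plus a register of coach activity in the other. If women in the two arms used outside help equally, the intervention arm would still score at least as high, and higher as soon as one coach contact or referral was registered.

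The rule also mixes different things. A referral is advice to seek care, whereas the MCQ records care used. Adding the two counts some episodes twice and counts others that never took place. Contact with the coach is exposure to the intervention, not help sought outside it.

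At stake is the reading of the extra-help outcome, which bears on whether online self-help reduces or increases the need for other help. The primary outcome, FCRI severity at 3 months, is not touched.

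**Working it through.** The plan states no figure on this point, so there is none to reproduce. The check is mainly one of logic.

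**Step 1: in which arm can the addition arise?** The coach appears in the Intervention section, and Usual care makes the online self-help the only extra in the intervention condition. No other place offers a coach to usual-care women. That the addition is confined to one arm is an inference, but nothing in the article points the other way.

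**Step 2: can a referral and an MCQ item be the same episode?** The coach refers to the general practitioner or medical specialist. The MCQ content includes visits to the general practitioner and other providers, and Study design has healthcare use asked every three months. There are three cases for a referred woman, if the score is a count:

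| Case | Referral added | Visit on MCQ | Units scored | Same episode in usual care |
|---|---|---|---|---|
| Attends and reports the visit | 1 | 1 | 2 | 1 |
| Attends, does not report the visit | 1 | 0 | 1 | 0 |
| Does not attend | 1 | 0 | 1 | 0 |

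In every case the intervention arm scores one unit more than usual care would for the same behaviour. The article gives no rule for removing the duplicate.

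**Step 3: does a yes/no score remove the problem?** It removes the duplicate in the first row, since referral plus visit then counts once. It does not remove the other two rows, where a woman is scored as having used extra help in one arm and not in the other.

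**Step 4: illustration of size.** Inputs: 227 women per arm (Sample size calculation). Assumed, because the documents give no rates: a share r = 5–20% of intervention women referred once, and a share u = 50–100% of those who attend and report the visit.

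- Units added by referrals = 227 × r: 227 × 0.05 = 11.35 and 227 × 0.20 = 45.4, so about 11 to 45, against 0 in usual care.
- Of these, counted twice = 227 × r × u: 227 × 0.05 × 0.50 = 5.7 and 227 × 0.20 × 1.00 = 45.4, so about 6 to 45, or 0.025 to 0.20 per woman.

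Coach help other than referral would come on top, but there is no basis for a number. The direction of the distortion depends on none of these assumptions.

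**Step 5: does the augmented score reach the costs?** The addition is written under the extra-help outcome only. Secondary outcomes and Cost-effectiveness analyses take volumes from the MCQ without mentioning it, and the latter keeps intervention costs apart from other healthcare costs. No sentence says that the augmented score is costed, and none says that it is not.

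**The case against.** Several arguments on the other side are sound.

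- **Costs.** A reader might infer that healthcare costs are double-counted and that the hypothesis of lower costs with self-help is biased. The documents do not support this. The rule belongs to another outcome, and the cost section's separation of intervention costs from other healthcare costs points away from it. If any excess did reach the costs, it would work against that hypothesis and not in its favour.
- **Technical assistance.** A reader might also infer that technical e-mails are counted twice. Technical assistance is not shown to be an MCQ item. Adding it would make the score asymmetric but would not duplicate anything, and the article does not say whether it falls under coach help for this purpose.
- **No specified contrast.** The Aims and Statistical analysis sections name no between-arm test of extra-help use. Extra help appears in the secondary aim, on who benefits from the training and who needs more. For that purpose a coach referral is a reasonable sign that self-help was not enough.
- **A true difference.** Coach contacts do not exist in usual care, so recording them reflects a real difference in what was received.
- **Level of detail.** How the score is built in full may be set out in a document not shown.

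The first two limit the point to the extra-help outcome. The third makes the harm conditional on a comparison being made, but a score carrying this name, collected in both arms, invites one. The fourth holds for coach contact as exposure to the training; it does not hold for referrals, where the care they lead to can be used in both arms and is already on the MCQ. The fifth does not answer a rule that the article states outright.

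**Conclusion.** The point holds for use of extra (psychological) help. The article fixes a scoring rule that in practice can add units in the intervention arm only. It makes the score not like for like, and it allows a referral to be counted twice or to be counted when no care was used. The double count requires the score to be a count; the asymmetry does not.

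The size is unknown. The 11 to 45 added units rest wholly on assumed referral rates and one referral per referred woman. Double-counting of costs, and bias in the cost hypothesis, remain a risk that the wording leaves open. This is a modest correction to an outcome listed under Other outcomes.

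**What to change.** Replace the rule under Other outcomes with four statements:

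1. Coach contacts and referrals are registered but are not added to the MCQ score.
2. The unaugmented MCQ, identical in both arms, is used for any between-arm comparison of extra-help use and for healthcare costs.
3. Coach contacts and referrals are reported separately, as intervention-arm process data alongside the login and website data. They remain available there for describing who needed more than self-help.
4. Coach time is costed once, within the intervention costs.

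The change costs wording only. The register is still kept, no data are lost, and neither the sample size nor the assessment schedule is affected.

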### Sample size calculation

The sample size calculation is based on a clinically relevant improvement on the FCRI severity subscale at 3 months. With an effect size of *d* = 0.3, a minimum number of 2.28 points on the FCRI severity subscale could be detected. Based on our experience with the FCRI, this seems to be a clinically relevant difference. In total 454 patients need to be included (227 in each group) to statistically detect the minimum effect size of *d* = 0.3 between mean FCRI severity subscale scores of both groups with a power of 0.8 and a two-sided alpha of 0.05. The power analysis program G*Power 3.1.7 was used to calculate the effect sizes [64]. Since in previous online intervention studies amongst breast cancer patients about half of all invited patients expressed an interest in participating and another 35 % was lost after randomization [65, 66], the aim of this study is to ask a minimum of 900 patients to participate in the study.

### Statistical analysis

#### Primary analyses

Baseline characteristics in both groups will be compared to check if randomisation has resulted in an equal distribution of the baseline variables. Data will be analysed according to the intention-to-treat (ITT) principle. In the primary analyses, post-training scores will be compared between the two groups, controlling for baseline symptom levels. Analyses will be performed using t-tests and linear mixed models including exploratory predictor analyses. An advantage of linear mixed models is the optimal use of available data. The primary analysis is aimed at comparing the online self-help with care as usual at 3 months on the FCRI severity subscale. Analysis of co-variance will be performed to test whether the outcome variables differed between the online self-help and care as usual, using baseline level as covariate. The stability of the results will be analysed using the data from 9 months and 24 months after baseline, again using linear mixed models to control for the dependency caused by the repeated measurements. Time will be analysed as a categorical predictor with four levels (baseline - 3 months - 9 months - 24 months). Linear mixed models with a specified covariance pattern model will be used to examine the course of FCR [67]. The fixed-effects parameters of the models will be estimated with maximum likelihood. Inspection of the Log likelihood ratio test, Akaike Information Criterion (AIC), and Bayesian Information Criterion (BIC) with restricted maximum likelihood (REML) will be used to find most suitable covariance pattern model (e.g., compound symmetry, autoregressive, unstructured).

For the secondary analyses, significant predictors will be selected using exploratory predictor analyses. Then multivariate hierarchical regression analysis will be performed to assess predictors of effect. The predictors that are found statistically significant will be added as interaction terms with condition (online self-help versus care as usual). Drop outs (attrition) will be closely investigated and predictors of drop outs will also be analysed by multivariate regression analysis.

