### Study design

The CAREST-study is a multi-centre, randomised controlled trial, comparing online self-help training with care as usual in breast cancer survivors. A sample of 454 women with curatively treated breast cancer will be recruited from 8 hospitals scattered over the Netherlands. The participating hospitals are the Maasstad hospital in Rotterdam, St Antonius hospital in Utrecht, Admiraal de Ruyter hospital in Vlissingen, Reinier de Graaf hospital in Delft, Antonius hospital in Sneek, St. Elisabeth hospital in Tilburg, Catharina hospital in Eindhoven, and UMCG in Groningen (all situated in the Netherlands). After completion of the baseline measure, women will be randomised to either the online self-help or control group. Follow-up assessments are at 3 months (post-intervention), 9 months, and 24 months after baseline. Additionally, every 3 months participants will be asked to fill out a short measure about their healthcare use. Two reminders will be sent by e-mail one and two weeks after the first invitational e-mails. Eventually, participants who do not complete the questionnaires will receive a phone call from the researcher to remind them.

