### Recruitment settings and procedure

Patients will be recruited in two ways. First, four hospital sites are expected to recruit participants through oncology nurses, nurse practitioners, or oncologists, who will ask eligible patients to participate in the study. These patients will be informed about the study during their regular check-up at the outpatient clinic. When women show interest in participating in the study, they receive a comprehensive information letter. In three hospitals patients will be phoned by the researcher two weeks after receiving the information letter. They will be asked whether they have any questions and if they are interested to participate in the study. Second, the remaining four hospital sites are expected to recruit participants by a comprehensive information letter sent to them by mail. These patients will also be phoned by the researcher about two weeks after receiving the information letter to ask whether they are interested to participate in the study. When patients decide to participate, they are asked to return the included informed consent form with the reply-paid envelope within a week. Moreover, all participants will be informed about the possibility for psychological counseling nearby, so they know where to turn to in case they need (more) help.

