### Randomisation

After completing the baseline measure, every patient will be randomly assigned to either the online self-help training or care as usual with an allocation ratio of 1:1. Block randomisation (block size 10) will be carried out through a sealed envelope system, for each hospital separately. Both the participants and the researchers are blinded for the randomisation process, but not for the randomisation outcome. Statistical analysis will be done by a statistician blind for randomisation outcome.

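### Randomisation is blocked by hospital, but the described primary model does not include hospital; if hospitals differ after baseline adjustment, the analysis is slightly conservative

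*Protocol article*

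**What the plan says.** The Randomisation section states: "Block randomisation (block size 10) will be carried out through a sealed envelope system, for each hospital separately", and allocation is "with an allocation ratio of 1:1". Under Study design, participants "will be recruited from 8 hospitals scattered over the Netherlands". Hospital is therefore a stratification factor with 8 levels.

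The Primary analyses section defines its target: "The primary analysis is aimed at comparing the online self-help with care as usual at 3 months on the FCRI severity subscale". It then describes an analysis of covariance testing the difference "between the online self-help and care as usual, using baseline level as covariate". The 9- and 24-month data are analysed "again using linear mixed models to control for the dependency caused by the repeated measurements", which refers to dependency within a participant. The section also sets the levels of time, the estimation methods and the criteria for choosing a covariance structure. Hospital is not mentioned there as a fixed effect, a random effect or a sensitivity analysis.

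Two other sections bear on whether hospitals might differ. Usual care says: "Care as usual may differ somewhat between hospitals and may include psychosocial care from within the hospital or elsewhere". Recruitment settings and procedure says that four sites recruit through clinic staff, while "the remaining four hospital sites are expected to recruit participants by a comprehensive information letter sent to them by mail".

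**The concern.** An analysis should normally reflect the restrictions placed on the randomisation. Blocking within hospital forces near-equal arms in each hospital, so differences between hospitals largely cancel out of the treatment contrast. A model without hospital does not know this. It leaves those differences in the residual and reports a standard error for a less well balanced trial than the one that was run. Confidence intervals become wider than they need be and some power is lost.

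Precision matters in this trial: the Aims section expects small effects, and the Sample size calculation cites 35% loss after randomisation in earlier online studies.

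**Working it through.** **Inputs from the article.** 8 hospitals; blocks of 10 within hospital; 1:1 allocation; 454 women; baseline score as covariate; d = 0.3 equal to 2.28 points, so the implied SD is 2.28 / 0.3 = 7.6; cited loss after randomisation 35%.

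**Assumed.** The article gives no between-hospital variance, so there is no figure of its own to reproduce on this point. Let ρ be the hospital share of the residual variance of 3-month FCRI severity *after* baseline adjustment. I show 0.01, 0.05 and 0.10. The simulation also assumes a baseline–outcome correlation of 0.6. The total of 454 is taken as stated. A two-sample t-test at d = 0.3 gives 176 per arm, 352 in all, but that is a separate matter and does not affect this point.

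**Step 1: closed form.** With exact balance within hospital, the true variance of the contrast is proportional to 1 − ρ, while the model without hospital estimates it as proportional to 1. The ratio of reported to true standard error is 1/√(1 − ρ):

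- ρ = 0.01: 1/√0.99 = 1.005 (0.5% too large)
- ρ = 0.05: 1/√0.95 = 1.026 (2.6%)
- ρ = 0.10: 1/√0.90 = 1.054 (5.4%)

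**Step 2: simulation of this design.** 8 near-equal hospitals, 454 women, permuted blocks of 10, ANCOVA on baseline with and without a fixed hospital effect; 6000 null runs and 4000 runs under an effect. The effect was 0.2642 × 7.6 × 0.8 = 1.61 points (0.8 = √(1 − 0.6²)), chosen to put power near 80%.

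| ρ | Mean model SE, without / with hospital | Ratio | Type I error, without / with | Power, without / with |
|---|---|---|---|---|
| 0 | 0.571 / 0.571 | 1.000 | 0.048 / 0.049 | 0.809 / 0.807 |
| 0.01 | 0.570 / 0.568 | 1.004 | 0.048 / 0.048 | 0.802 / 0.806 |
| 0.05 | 0.570 / 0.557 | 1.022 | 0.047 / 0.053 | 0.815 / 0.825 |
| 0.10 | 0.568 / 0.542 | 1.047 | 0.042 / 0.048 | 0.819 / 0.848 |

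The Monte Carlo error of a type I rate near 0.05 is √(0.05 × 0.95 / 6000) ≈ 0.003, so the rows at 0.01 and 0.05 cannot be told apart from 0.05. The simulated ratios lie a little below the closed form. With only 8 hospitals the overall intercept absorbs about one eighth of the hospital variance: √((1 − ρ/8)/(1 − ρ)) gives 1.004, 1.023 and 1.047.

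At ρ = 0.10 under the null, the mean reported standard error without hospital is 0.568 against a true SD of the estimate of 0.546. With hospital it is 0.542 against 0.545, so the mismatch closes.

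**Step 3: loss after randomisation.** Suppose 35% are lost at random and the analysis uses those observed. For a hospital of m women, the difference in arm sizes then has variance m × 0.65 × 0.35. Unrestricted randomisation of the 0.65m who remain would give 0.65m. A fraction 0.35 of the hospital variance therefore re-enters the contrast, and the true variance is proportional to 1 − ρ + 0.35ρ = 1 − 0.65ρ. The ratio of reported to true standard error falls to 1/√(1 − 0.65ρ): 1.003, 1.017 and 1.034 at ρ = 0.01, 0.05 and 0.10.

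**The case against.** The strongest reply is that this is a condensed article. It says the baseline level is a covariate; it does not say it is the only one. Site terms are often left to a full protocol or analysis plan, neither of which is shown. This limits confidence: if either document already includes hospital, the point is closed. It does not remove the point, because the section is detailed enough to describe a model, down to estimation method and covariance selection, and that model omits the one factor used in the randomisation. The section also names t-tests beside the ANCOVA and mixed models, but no hospital term is given for any of them.

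A second reply concerns the evidence for hospital differences, and most of it stands. The Usual care section says only that care may differ somewhat. Recruitment route acts before the baseline measure, so much of any difference in case mix should already be captured by the baseline score. The share that matters is what remains after baseline adjustment, and it may be small.

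Two stronger readings are tempting, and the article supports neither. A reader might infer that the standard errors *are* too large because hospitals really differ; nothing in the article quantifies this, and at ρ = 0 the two models agree. A reader might also infer that type I error falls materially below 5%, or that a sizeable part of the sample is wasted. Those figures need a residual share near 10% and, for the type I error, exact balance within hospitals among those analysed, which loss on the cited scale would disturb.

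**Conclusion.** The point holds in a limited, conditional form. The described primary model omits the factor by which randomisation was blocked. To the extent that hospitals differ in 3-month FCRI severity after baseline adjustment, the reported standard error is somewhat too large and the test slightly conservative.

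For an assumed residual hospital share of 1% to 5%, the excess is about 0.5% to 2.6% and the loss of power about 0.4 to 1.0 percentage points. At 10% the excess is about 5% and the loss about 3 points. These figures assume near-complete balance within hospitals; with 35% random loss, the gap between reported and true standard error is about a third smaller.

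The treatment estimate is not biased and the false-positive rate is not raised, so the omission does not threaten a positive conclusion. This is a cheap improvement, not a flaw that undermines the trial.

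**What to change.** State in the analysis section, before the data are analysed, that hospital enters the primary 3-month model and the longitudinal mixed model alongside the baseline score. Either a fixed effect with 8 levels or a random intercept is acceptable; choose one in advance.

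The cost is one sentence and, for the fixed effect, 7 degrees of freedom: 454 − 3 = 451 residual degrees of freedom become 444. With the cited 35% loss, about 295 women would remain (454 × 0.65), and 7 degrees of freedom would still be negligible. If hospitals turn out not to differ, the simulation at ρ = 0 shows essentially no penalty (power 0.807 against 0.809). If the full protocol or analysis plan already contains the term, no change is needed beyond saying so.
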